# Trial design and methodology

## Description and justification of design

The study is a single centre randomised controlled and blinded study (observer blind). It will be conducted at the CNRFP Vaccinology unit located in Balonghin. Children in the catchments area within the 1-2 years age group, whose parents consent will be screened to randomise 45 eligible participants.

Clinical, biological and immune response data gathered after vaccination with 15µg and 30µg MSP 3 LSP will be compared to:

- The children’s baseline data before vaccinations, and
- The post vaccination data of children in the control group.

Randomisation will ensure that the comparison groups are similar in relevant characteristics at baseline. The concealment of allocation before enrolment will further enforce the randomisation. Individuals who will make the assessment of the study end points will be completely blinded of the vaccine administered. This will ensure that there is no observer bias. Further, reporting or information bias will be minimised, because the recipients will also not be aware of which vaccine they have been administered. This is possible because the selected control vaccine has not been in routine use in this area, and has only now been recommended by the Ministry of Health. Cross over immunisation at the end of the trial will involve only those children who will received the study vaccine; they will be administered the control vaccine in the interest of public health benefits for them.

The schedule of vaccination at 0, 1 and 2 months has been adopted because it is suitable for the target group. The idea is to eventually deploy the vaccine through the expanded programme on immunisation should the vaccine become registered for public use. For the EPI age group, it is not only an efficient delivery mechanism, but they are also the most vulnerable group to malaria.

## Study Site

This study will be conducted by the PDVAP/CNRFP. The team at this centre received a grant specifically to build their capacity for undertaking malaria vaccine trials. They have recently built a Vaccinology unit at their field site in Balonghin (50km south of Ouagadougou), which is specifically designed for vaccine trials. The PDVAP/CNRFP has further established demographic surveillance system within Saponé district (100,000 inhabitants living 79 villages around Balonghin). Through this system, data on vital events and basic malariometric parameters have been collected for a deeper and reliable baseline data necessary for potentials malaria phase 2 or 3 vaccines trials.

At the Vaccinology unit, facilities exist for screening many participants, medical examination, blinded randomisation and treatment allocation. There are observation rooms and resuscitation facilities necessary for post vaccination evaluation and treatment of immediate reactions following immunisation. A laminar flow hood is installed for extemporaneous mixing of vaccine with adjuvant. There is constant radio communication available between the site and Ouagadougou where there is the main tertiary hospital. The team has a fully equipped ambulance and 4X4 motor vehicle transport. The PDVAP/CNRFP team has been working in this area for over five years now, and have established a very good relationship with the community. In short, the team is adequately staffed and equipped to conduct this study.

# Conduct of the trial

## Recruitment procedure

From the up to date database of the population in the study area, a list of all children 1-2 years old will be drawn. Parents of selected child will be visited at home by field workers who will discuss the study with them; an invitation letter will be given for them to come to the field station of PDVAP to receive more information about the study. In informed consent procedure will be instituted which will have several levels of authorisations starting from the civil authorities to the local village leadership and down to small groups and ultimately individual parents/guardians. Those who provide a signed informed consent will be screened for study eligibility. A total of 45 eligible children will enrolled

These will further be invited to provide signed and witnessed informed consent before actual enrolment and administration of the study vaccine.

## Randomisation and treatment allocation

### Randomisation of participants

The study statistician will produce a randomisation list before the trial starts. This list will have the exact treatment and dosage allocated to each unique study ID number. The randomisation list for each group will be independent from the other. Subjects will be allocated sequentially to treatment numbers in the order that they present for vaccination.

### Method of blinding and breaking the study blind

Data pertaining to the trial will be collected in a double blinded (observer blinded) manner. “Double blinded (observer blinded)”in this context means that the vaccine recipient and their parent(s)/guardian(s) as well as those responsible for the evaluation of safety and immunogenicity endpoints will all be unaware the exact treatment, (MSP3 or Hepatitis B)given to the participant. The only study staff aware of the vaccine assignment for Hepatitis B or MSP3 will be those responsible for the storage and preparation of vaccines; these staff will play no other role in the study.

. Sealed envelopes labelled with the study ID number and containing the treatment allocated to each particular ID number will be provided to the investigator. The clinical investigator will only be allowed to open an envelope after ensuring that the child before him has met all eligibility criteria and has been given the study ID number. For each child, eligibility will have to be counter checked and signed by a second person before allocation of study ID number.

All envelopes will be retained to be checked by the clinical monitor.

The local safety monitor who is independent from the study team will also be provided a sealed randomisation list corresponding to each group. In total, 2 sealed randomisation list will be provided. If deemed necessary for reasons such as safety, the Local Safety Monitor in Ouagadougou as well as AMANET Central Safety will unblind the specific enrolled subject without revealing the study blind to the investigators.

As part of the safety monitoring plan, safety reports will be produced at 5 timepoints in the trial. An independent statistician will analyze the data, thereby maintaining the blind of the investigator group.

A formal reporting and analysis plan (RAP) will be developed. Once the study is completed and the database locked. AMANET will be responsible for initiating the execution of the statistical analysis plan in collaboration with the investigator team and breaking the blind.

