| **Primary**  **Evaluation Criteria** | The primary endpoints are measures of the safety and reactogenicity of the vaccine as determined by:   1. Occurrence of solicited symptoms during a 7 day follow-up period after each vaccination (day of vaccination and 6 consecutives days) 2. • Occurrence of unsolicited symptoms during a 28 day follow-up period after each vaccination 3. • Occurrence of serious adverse events throughout the study period |
| **Secondary Evaluation Criteria** | 1. **Humoral response to vaccine antigens:**   Post vaccination levels of IgG, IgA and IgM, expressed in arbitrary units (ng/ml), relative to the pre-vaccination level (D0): D28/D0, D56/D0, D84/D0, D168/D0, and D365/D0.   1. **Cellular immune response to vaccine antigens:**   The number of cells producing IFNγ by Elispot expressed in number of spots /106 cells |
| **Exploratory Evaluation Criteria** | **To evaluate IgG ability to recognise the native protein on Merozoite by using WB**   - **Parasite inhibition by ADCI (SGI %) on D0, D84, D168 and D365. (only if isotype study shows the production of MSP3 specific cytophilic Abs in > 30% of volunteers)** |
| **Statistical Methods** | The analysis shall be descriptive  The final analysis is planned 1 month post Dose 3 to evaluate whether the safety GO/No GO criteria are met to proceed to a phase 2b in. An annex safety analysis will be performed at the end of the study, 9 months post Dose 3. |

| Study phases | Screening | Vaccination Phase (Double blind) | | | | | | | | | | Follow up (Single blind) | | |
| --- | --- | --- | --- | --- | --- | --- | --- | --- | --- | --- | --- | --- | --- | --- |
| Clinic Visit | **V1** | **V2** |  | **V3** | **V4** |  | **V5** | **V6** |  | **V7** | **V8** | **V9** |  | **V10** |
| **Home visits1** |  |  | **HV1-5** |  |  | **HV6-10** |  |  | **HV11-15** |  |  |  | **HV16-21** |  |
| **Trial Timelines (Days,)** | **D-28** | **D0** | **D1-D5** | **D6** | **D28** | D29-D35 | **D36** | **D56** | **D57-D62** | **D63** | **D84** | **D168** | **D196-D337** | **D365** |
| **Time Windows (Days)** |  |  4 D |  |  |  4 D |  |  |  4 D |  |  |  4 D |  7 D |  7 D |  14 D |
| **Study procedures** |  |  |  |  |  |  |  |  |  |  |  |  |  |  |
| Screening consent |  |  |  |  |  |  |  |  |  |  |  |  |  |  |
| Study Consent |  |  |  |  |  |  |  |  |  |  |  |  |  |  |
| Check of inclusion /non Inclusion Criteria |  |  |  |  |  |  |  |  |  |  |  |  |  |  |

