## Data processing

The principal investigator will review and approve of the CRF pages for data entry. The data base for this study is created in Microsoft Access® software and shall be entered by two separate data entrants. The supervising data manager will do all the data reconciliations and validations leading to the validated file for each participant. The database is designed to keep track of all entries in time and password and will be able to provide a complete audit trail.

Any illegible CRF entries will be sent back to the clinical investigators with accompanying appropriate data query form. The monitor will also routinely check the database against the CRFs, and will ensure that all accumulated data query resolutions are verified as consistent on the database, CRF and source document.

Regular reports will be compiled for presenting to the DSMB for their ongoing review of safety data. This shall be in a blinded manner. The final analysis will be done immediately after day 84 to allow for phase IIb study Go/No go evaluation.

At the end of the study, all data queries will be resolved, data cleaned and accepted before database locking. After database lock, no further entry shall be possible, and this is set for month 14.

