### Assessment of causal relationship

The causal relationship between the SAE and the product will first be evaluated by the investigator using the following scale:

**0.** **NO RELATIONSHIP**: Inconsistent temporal relationship (too long interval between injection and onset of symptoms or symptoms appeared before injection) or evidence that symptoms are definitely related to an aetiology other than the study treatment.

**1.** **POSSIBLE**: Has a temporal relationship with the study treatment; however, a potential alternative aetiology which may be responsible for the symptom has not been investigated.

**2.** **PROBABLE**: Has a **relevant** temporal relationship to the study treatment, a suggestive symptomatology and a potential alternative aetiology is not apparent.

**3. DEFINITE**: Has a **relevant** temporal relationship to the study treatment and no alternative aetiology is apparent (after investigation other aetiologies have been ruled out) or positive rechallenge with a suggestive symptomatology or local reaction at the site of injection.

Then, according to the available information and the current medical knowledge, the Sponsor will also assess the causal relationship to the product.

The decision to modify or discontinue the trial, or all study codes may be made after mutual agreement between AMANET and the investigator(s) and the DSMB.

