# Statistical Methods and Data Analysis

## Principal Objective

To assess the safety and reactogenicity of 3 doses of 30 µg and 15 µg MSP3 adjuvanted in aluminium hydroxide given at D0, D28 and D56 in healthy children aged 4-6 and 1-2 years old in Burkina Faso.

This will be achieved through conducting a randomised controlled trial. The trial will certainly be single blinded to the participants. Efforts will be made towards a double blind design in that concealment of vaccination will be ensured to all who will be involved in the objective assessment of trial endpoints.

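### Section 5.2.2 contradicts itself on who may know the allocation: followed literally, the envelope step reveals MSP3 or hepatitis B to the investigator role that judges adverse events

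*Protocol*

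**What the plan says.** Section 5.2.2 of the protocol (Method of blinding and breaking the study blind) defines the trial as observer-blind. Recipients, parents and those who evaluate safety and immunogenicity are not to know whether MSP3 or hepatitis B was given. Only the people who store and prepare vaccine may know, and "these staff will play no other role in the study".

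The next paragraph of the same section reads: "Sealed envelopes labelled with the study ID number and containing the treatment allocated to each particular ID number will be provided to the investigator". It continues: "The clinical investigator will only be allowed to open an envelope after ensuring that the child before him has met all eligibility criteria" and has received a study ID. A second person countersigns eligibility before the ID is given.

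Elsewhere the protocol gives the investigator these tasks:
- Section 13.4.2: enter every adverse event in the case report form, with intensity and relationship to vaccine.
- Section 13.4.2.3: the causal relationship of a serious adverse event "will first be evaluated by the investigator", and then by the sponsor.
- Section 14.1: determine relationship to vaccine within the primary evaluation criterion.

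Section 4.1 promises that endpoint assessors are fully blinded. Section 16.1 says of observer blinding: "Efforts will be made towards a double blind design". The flow chart in the Synopsis heads the period after D84 "Follow up (Single blind", and the scheme in section 3 uses the same label.

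**The concern.** The primary endpoint is safety and reactogenicity, and much of it is graded by judgement. If the person grading an event, or attributing it to vaccine, knows which vaccine the child received, the side-by-side picture of MSP3 and control can shift in either direction. Nothing later in the trial can undo that knowledge.

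Two suspension criteria in section 5.2.11 also draw on investigator judgements: a death or life-threatening event judged related to vaccine, and more than 5% of vaccinated children withdrawn by the investigator for reactogenicity. The second is sensitive to very few decisions. The section does not state the denominator. If it is one MSP3 arm of 15, one withdrawal is 1/15 = 6.7%. If it is all 30 MSP3 children, one is 3.3% and two are 6.7%.

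**Working it through.** The plan gives no figure on this point. The detection probabilities in section 16.2 do not depend on who opens the envelopes. The check is therefore a comparison of passages, followed by a count of what is exposed.

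**1. Can the two statements in 5.2.2 both be followed?** The first limits knowledge of the assignment to preparation staff with no other role. The second has the clinical investigator open a document that holds the assignment, with the child present. They conflict unless another passage narrows the second. Three readings could do so:
- *The envelope shows only a code.* Section 5.2.2 says it contains the allocated treatment, and the list described in 5.2.1 carries the exact treatment and dosage for each ID.
- *It is an emergency code-break envelope.* Opening is tied to eligibility and ID allocation. Unblinding for safety is given to the local safety monitor and the sponsor's central safety function, who are to do it without disclosing the code to investigators. That safeguard would serve no purpose if the investigator had already opened the envelope.
- *The opener is an investigator who assesses nothing.* No passage says so. The only staff separated from other tasks are those who store and prepare vaccine.

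None of the three is supported, so the contradiction stands.

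**2. Does the disclosure reach the primary endpoint?** Sections 13.4.2, 13.4.2.3 and 14.1 place documentation, intensity and causality with the investigator. Section 5.2.4 has a study clinician assess the child at the clinic on the sixth day after each dose. The link is through the role; the protocol does not identify the individual.

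**3. How much is exposed?**
- One envelope per child gives 45 children. With three doses each, 45 × 3 = 135 injections is the ceiling.
- By the text of 5.2.4, the seven-day solicited period has five days of home visits by field workers and two days of clinic contact (vaccination day and day 6). Direct clinic observation is therefore 2 of 7 days per dose.
- Events noted at home still pass through the investigator, because 13.4.2 has the investigator complete the case report form, including intensity and relationship.
- Of the nine solicited symptoms in 13.4.2.2, five use judgement scales (pain, pruritus, irritability, drowsiness, appetite). Four are measured in mm or °C (swelling, induration, erythema, fever).

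**4. The period after D84.** Section 5.2.2 breaks the blind after study completion and database lock, which section 6.3 sets at month 14. Section 19 opens the code only after the database freeze. The single-blind label in the two charts is not defined and does not fit these sections.

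**The case against.** The strongest reply is that the design intends blind assessors and says so repeatedly. Section 4.1 promises it, 5.2.2 defines it, safety unblinding is arranged to keep investigators blind, and the safety reports go through an independent statistician for the same reason. The Synopsis lists several investigators, so the person who opens an envelope need not be the one who grades events. This stands in part. It makes the point an internal contradiction, and it does not establish that any assessor is in fact unblinded. It does not remove the contradiction, because intent without a written separation leaves site staff with an explicit instruction to open the envelope.

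A reader might also infer four stronger things that the documents do not support:
- *That 16.1 abandons observer blinding.* The sentence goes on to say that concealment will be ensured for those who assess endpoints. It is awkward, but it is no retreat.
- *That the blind is broken a second time at D84.* Section 6.3 says: "The final analysis will be done immediately after day 84 to allow for phase IIb study Go/No go evaluation". An early analysis does not in itself tell investigators the allocations, and no passage says that they learn them then. Who runs it may be settled in the reporting and analysis plan that 5.2.2 announces. Nor do the 365 − 84 = 281 days add to the exposure. If the investigator knows the treatment from enrolment, they are already included; if not, nothing shows that the blind is lost in them.
- *That the Go/No-Go decision rests on compromised judgements.* Its criteria are mentioned but never stated.
- *That every symptom record is affected.* Field workers make the daily home visits and are not shown to see an envelope, and four of the nine symptoms are measured.

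Two further limits are fair. Section 16.4 makes the analysis descriptive, so no formal test is at stake, although 4.1 still sets MSP3 against control. Suspension does not hang on the investigator alone, since the sponsor also assesses causality and the DSMB reviews unblinded data.

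**Conclusion.** The point holds as an internal contradiction in section 5.2.2 and should be corrected before the first child is enrolled. Followed literally, the envelope procedure tells the investigator role which vaccine each of the 45 children receives, and that role documents and attributes the events that form the primary endpoint. The likely reach is clinic assessments, case report form entries on intensity and relationship, and causality. The direction and size of any bias cannot be computed from the protocol.

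The conclusion assumes that the envelopes hold what 5.2.2 says they hold and that no unseen procedure bars the opener from assessment. If an SOP already does so, the protocol text still needs to match it. The single-blind label after D84 is a secondary labelling inconsistency.

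**What to change.** - **Section 5.2.2:** state that only the already unblinded vaccine-preparation staff hold and open the allocation envelopes, one at a time, after eligibility has been signed and countersigned. The investigator sees only the study ID. Keep the present order (eligibility, ID, opening), which protects concealment. Name envelope custody as part of the preparation staff's duties, so that the sentence giving them no other role remains true. Keep opened envelopes with them for the clinical monitor's check.
- **Section 16.1:** replace the wording on efforts with the observer-blind definition in 5.2.2.
- **Flow charts (Synopsis and section 3):** replace the single-blind label after D84 with a statement that assessors stay blind until database lock, in line with 5.2.2 and section 19.

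The cost is wording in these places and a change in who keeps the envelopes. There is no new staff, no change in sample size and no change in the care of the children.

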### Trial Calendar

Screening for potential study participants is planned to start in February 2007. The first participant is planned to be recruited in March 2007. The recruitment period will last for four weeks. Vaccinations would then start in March, and will be staggered starting with Lower dose of MSP3 (15 µg) and then the Higher dose (15 µg) 14 days later. Each participant will be followed-up for a total period of one year from the first injection. The study has 11 scheduled clinic visits and 21 scheduled home visits, but participants will be under strict instructions to report at the unit should they feel unwell at any time. The planned final analysis at 1 month post vaccination 3 will look only at safety data to evaluate the go/no go safety criteria for pursuing the clinical development plan.

### Vaccination and serological schedule

Scheduled clinic visits are planned at day -28, 0, 6, 28, 36, 56, 63, 84, 168 and 365. Three vaccine doses will be administered by subcutaneous injection (day 0, 28 and 56). As shown in the flow chart (see page 9), participants will be monitored for the hour following vaccination, then a field worker will visit them at home on each of the 5 days following the injection. The patient will come back to the clinic at the 6th day following each immunization to be assess by a study clinician. Six serological blood sampling points have been planned on days 0, 28, 56, 84, 168 and 365.

Biological evaluations will also be done on days -28, 0, 6, 28, 36, 56, 63, 84 and 365. Apart from these standard examinations, other tests may be performed if deemed necessary.

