| Medical History |  |  |  |  |  |  |  |  |  |  |  |  |  |  |
| Worm infestation treatent |  |  |  |  |  |  |  |  |  |  |  |  |  |  |
| Physical Examination |  |  |  |  |  |  |  |  |  |  |  |  |  |  |
| Check of contra-Indications to vaccination |  |  |  |  |  |  |  |  |  |  |  |  |  |  |
| Randomisation |  |  |  |  |  |  |  |  |  |  |  |  |  |  |
| Vaccine administration |  | **** |  |  | **** |  |  | **** |  |  |  |  |  |  |
| Check of elimination criteria |  |  |  |  |  |  |  |  |  |  |  |  |  |  |
| Recording of medication |  |  |  |  |  |  |  |  |  |  |  |  |  |  |
| **Safety and reactogenicity data collection** |  |  |  |  |  |  |  |  |  |  |  |  |  |  |
| Immediate post-vaccine surveillance (60’) |  | x |  |  | x |  |  | x |  |  |  |  |  |  |
| Recording of solicited Local & Systemic Events/Reactions |  |  | x | x | x | x | x | x | x | x |  |  |  |  |
| Recording of unsolicited adverse events |  |  |  |  |  |  |  |  |  |  |  |  |  |  |
| Recording of Serious Adverse Events |  |  |  |  |  |  |  |  |  |  |  |  |  |  |
| **Laboratory analysis** |  |  |  |  |  |  |  |  |  |  |  |  |  |  |
| Complete blood count |  |  |  |  |  |  |  |  |  |  |  |  |  |  |
| Creatinine, ALT/AST, Biluribin |  |  |  |  |  |  |  |  |  |  |  |  |  |  |
| Humoral response measurement |  |  |  |  |  |  |  |  |  |  |  |  |  |  |
| Cell mediated immunity measurement |  |  |  |  |  |  |  |  |  |  |  |  |  |  |
| Functional assays (ADCI) |  |  |  |  |  |  |  |  |  |  |  |  |  |  |
| Anti-HBs antibodies |  |  |  |  |  |  |  |  |  |  |  |  |  |  |
| Western blot |  |  |  |  |  |  |  |  |  |  |  |  |  |  |
| **Analysis and reporting** |  |  |  |  |  |  |  |  |  |  |  |  |  |  |
| Final Analysis |  |  |  |  |  |  |  |  |  |  |  |  |  |  |
| Annex safety Analysis |  |  |  |  |  |  |  |  |  |  |  |  |  |  |

**1**  from the first home (HV1) to HV15 the visit will be daily. The visits wil be monthly from HV16 to HV21

| **List of Abbreviations** |
| --- |

95% CI 95% Confidence Interval

AIDS Acquired Immunodeficiency Syndrome

AMANET African Malaria Network Trust

ADCI  Antibody Dependent Cellular Inhibition of parasite growth assay

CRF  Case Report Form

CNRFP Centre National de Recherche et de Formation pour le Paludisme

CTA Centre des Traitements Ambulatoires

DSMB Data and Safety Monitoring Board

EC  Ethics Commitee

ELISA Enzyme Linked Immuno Sorbent Assay

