## Clinical experience with MSP 3 LSP

**A first phase 1a trial** was conducted in Switzerland, on healthy adults, who had never been exposed to malaria. The MSP3-LSP vaccine was administered to 35 volunteers, in 3 subcutaneous injections at 0, 1 and 4 months. Four different dosages: 10µg, 20µg, 30µg or 100µg and two adjuvants, Montanide 720 and Aluminium hydroxide were evaluated. The following table shows the distribution of subjects by dose and by adjuvant:

| **Groups** | **Dosage** | **Adjuvant** | **Number of subjects** |
| --- | --- | --- | --- |
| M10-10-10 | 10 µg LSP | Montanide 720 | 6 |
| M30-30-10 | 30 µg LSP | Montanide 720 | 6 |
| M100-10-10 | 100 µg LSP | Montanide 720 | 5 |
| M20-20-20 | 20 µg LSP | Montanide 720 | 6 |
| A30-30-30 | 30 µg LSP | Alum | 6 |
| A100-10-10 | 100 µg LSP | Alum | 6 |

Immediate local and systemic tolerance was monitored for the hour following the injection and again two days after vaccination. Humoral and cellular immune responses and the functionality of the immune response were assessed one month after each injection and five and nine months after the booster dose.

The vaccine showed a very good systemic tolerance, whatever the adjuvant or dose, with no systemic reactions observed during the study. In contrast, local tolerance was clearly linked to dose, adjuvant and injection number. Because of large local reactions, with 10cm indurations, the second scheduled 100µg injections were replaced by 10µg injections for both adjuvants. After the second 30µg MSP3, Montanide adjuvated dose, the increasing local reactions observed led the investigator to replace the third dose with a 10µg dose. With a 30µg MSP3 vaccine adjuvanted with Aluminium hydroxide, the growing number of local reactions only emerged after the third dose had been delivered. (See following figures).

[figure not shown]

The immune response induced by MSP3’s different formulations in humans, was higher than the response observed in pre-clinical studies. Interestingly, the adjuvant effect of aluminium hydroxide in humans was greater in humans than in monkeys or mice, and it was comparable to the adjuvant effect of Montanide 720. The immune response was maintained nine months after the booster dose was injected. The functionality of the immune response, as measured by the ADCI assay, showed that antibodies induced by vaccination could lead to an inhibition of *P. falciparum.*

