|  | **SCREENING** | | | | | | | **VACCINATION** | | | | | | | | | **LONG TERM SAFETY FOLLOW UP** | | |  |
|  |  | | | | | | | **DOUBLE-BLIND PHASE** | | | | | | | | | **SINGLE-BLIND PHASE** | | |  |
|  |  | | | | |  |  |  |  | |  | |  | |  | |  |  | |  |
| **BS;** Blood Sample. **Vacc;** Vaccination. | | | | | | | | | | | | | | | | | | | | |
|  | | | | | | | | | | | | | | | | | | | | |

- Double blind (observer blind, participant blind), randomized, controlled, dose escalation, Age de-escalation, phase Ib study
- One study centre,
- Two parallel groups
- Group 1: 23 subjects (15 subjects receiving MSP-3 vaccine 15 µg and 8 subjects receiving Hepatitis B vaccine).
- Group 2: 22 subjects (15 subjects receiving MSP-3 vaccine 30 µg and 7 subjects receiving Hepatitis B vaccine)
- Immunization schedule will be 0, 1, and 2 months for all cohorts and provisionally as following for each group:
  - Study days 0, 28 and 56 for group 1
  - Study days 14, 42, 70 for group 2
- Vaccinations of groups 1 and 2 will be staggered: immunization in group 2 will start 2 weeks after group 1. This interval may be extended if deemed necessary due to SAEs or other safety concerns.
- Randomization will be done for each group at the times of first vaccinations.
- Route of inoculation will be by subcutaneous injection into right or left deltoid (alternately).
- Each child will be observed for at least 60 minutes after vaccination to evaluate and treat any acute adverse events (AEs)
- Study duration will be approximately 13 months per subject.
- Seven (7) day follow-up period for solicited adverse events (day of vaccination plus 6 subsequent days)
- Twenty eight (28) day follow-up period for unsolicited adverse events (Vaccination day plus 27 subsequent days)
- Follow-up of serious adverse events (SAE’s) for 12 months after the first dose of study vaccine (9 months after dose 3)
- At the end of the follow-up period for unsolicited AEs (i.e., one month after the third dose), subjects will be followed by field workers at home at monthly intervals to record SAEs.
- Data collection: conventional Case Report Form (CRF).

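### The listed post-dose visit days (+6, +8 and +7 days) contradict the protocol's own rule of five daily home visits and a day-6 clinic visit after every dose

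*Protocol*

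**What the plan says.** **Doses.** Section 5.2.4 (Vaccination and serological schedule): "Three vaccine doses will be administered by subcutaneous injection (day 0, 28 and 56".

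**Calendar.** The same section: "Scheduled clinic visits are planned at day -28, 0, 6, 28, 36, 56, 63, 84, 168 and 365". It also ties laboratory evaluations to D6, D36 and D63. The Synopsis flow chart shows the same three clinic days and sets HV1-5 on D1-D5, HV6-10 on D29-D35 and HV11-15 on D57-D62.

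**Rule in words.** Section 5.2.4 says of the children: "then a field worker will visit them at home on each of the 5 days following the injection". It continues: "The patient will come back to the clinic at the 6th day following each immunization to be assess by a study clinician". Section 5.2.5 (Clinical evaluation and follow up) repeats both parts. Footnote 1 to the flow chart adds: "from the first home (HV1) to HV15 the visit will be daily".

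**Window.** Section 3 (Study Design Overview): "Seven (7) day follow-up period for solicited adverse events (day of vaccination plus 6 subsequent days". The primary evaluation criteria in the Synopsis use the same window after each dose. Section 14.2.1.1 gives local reactions a 7-day period with a reference to D1 and D7. Section 14.2.1.2 runs systemic reactions from D1 to D6.

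**Recording.** The flow chart marks solicited recording at D36 and D63. Section 14.2.2 treats a solicited symptom that begins outside its period as unsolicited.

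**The concern.** Solicited reactions over 7 days after each dose are a primary criterion, with rate, duration and severity to be measured (section 14). The safety reports tabulate them separately for doses 1 and 2 (section 5.2.10), the pair with the largest difference in offset. The analysis is descriptive (section 16.4), so the raw frequencies are the result, and the analysis one month after dose 3 informs the go/no-go decision.

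The change from one dose to the next is of interest for this product. On the Swiss adult trial, the protocol reports that "local tolerance was clearly linked to dose, adjuvant and injection number". If observation also changes with dose number, part of any trend could come from the visit plan.

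A measurement that was never taken cannot be recovered at analysis. Section 13.4.2.2 grades swelling, induration and erythema by diameter in mm and fever by recorded temperature. A parent's later account does not fully replace either.

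**Working it through.** **Inputs.** Dose days 0, 28, 56 and clinic days 6, 36, 63 (section 5.2.4); home-visit ranges (Synopsis flow chart); window from the vaccination day to +6 (Synopsis, section 3).

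**Step 1: the protocol's own figure.** The rule in words puts the clinic visit at +6 after every dose. Clinic day minus dose day gives 6 - 0 = 6, 36 - 28 = 8 and 63 - 56 = 7. The stated figure is reproduced for dose 1 only. Applied to all doses, the rule would give D6, D34 and D62.

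**Step 2: home visits.** Five numbered visits per dose make 15, and HV16-21 add 6, giving the 21 home visits in section 5.2.3. The ranges contain 5, 35 - 29 + 1 = 7 and 62 - 57 + 1 = 6 days, or 18 in all. Fifteen daily visits cannot fill 18 days.

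**Step 3: overlap with the window.** Take five daily home visits starting the day after each dose, and the listed clinic days:

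| | Dose 1 | Dose 2 | Dose 3 |
|---|---|---|---|
| Window | D0-D6 | D28-D34 | D56-D62 |
| Clinic visit | D6 (+6) | D36 (+8) | D63 (+7) |
| Clinic visit relative to window end | on the last day | 2 days after | 1 day after |
| Home visits on days +1 to +5 | 5 | 5 | 5 |
| Contacts on days +1 to +6 | 6 of 6 | 5 of 6 | 5 of 6 |

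The gap is day +6 after doses 2 and 3. If D7 in section 14.2.1.1 means +7, D63 falls inside the window for local reactions. D36 is outside on any reading.

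**Step 4: illustration of size.** Assume a true risk of 15% per dose; this is an assumption that borrows one of the risks in section 16.2.
- *Downward.* One-day events are spread evenly over days +1 to +6 and seen only on contact days. Recorded risk is 15% x 6/6 = 15%, then 15% x 5/6 = 12.5% after doses 2 and 3.
- *Upward.* Everything up to the clinic visit is counted (7, 9 and 8 days) at a constant rate. Recorded risk is 15%, then 1 - 0.85^(9/7) = 18.9% and 1 - 0.85^(8/7) = 17.0%.
- *Yardstick.* The standard error with 15 children is sqrt(0.15 x 0.85 / 15) = 9.2 percentage points.

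The shift runs from -2.5 to +3.9 points, below one standard error. It could be nil with full recall and strict use of the window.

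**The case against.** The strongest reply is that the protocol prescribes identical follow-up after every dose, twice in words, so the listed days are a slip. This stands in part: the defect is a contradiction between two schedules. It does not remove the problem, because the uneven days appear in the clinic list, the laboratory list and the flow chart, which a site may well use as its calendar.

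A reader might infer more than the documents support:

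- *That follow-up is designed to differ by dose and that reactogenicity therefore shifts.* The uniform rule contradicts the first part. For the second, neither direction nor size can be established.
- *That a sign first seen at D36 or D63 becomes unsolicited.* Section 14.2.2 turns on onset, and section 13.4.2 requires the date and time of occurrence. A reaction that began on day +6 and was reported later stays solicited. The exposure is a brief event that is not recalled, or a size or temperature not measured that day.
- *That only 4 of 6 days are covered after dose 2.* This needs a home visit on D35, against the rule that the five visits follow directly after the injection.
- *That the arms are compared unfairly.* All arms share the calendar, so the comparison with hepatitis B at the same dose number is not affected.
- *That the blank D0 cell in the solicited-recording row is a gap.* Many rows of that table show no marks at all, probably lost in text extraction. The 60-minute surveillance row marks D0.

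**Conclusion.** The point holds as an internal contradiction with a possible effect on a primary criterion. The listed days give +6, +8 and +7; the stated rule gives +6 throughout. If the listed days are followed, the dose 2 examination is outside the solicited window on any reading. The dose 3 examination is outside it unless section 14.2.1.1 is read as reaching +7. Days +1 to +6 then have 6, 5 and 5 contacts, assuming daily home visits from the day after each dose.

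The exposure is limited to the pattern across doses 1, 2 and 3 and to the timing of post-dose laboratory values. The illustrative shift of -2.5 to +3.9 points rests on an assumed 15% risk and on simple event patterns. It shows scale only and is no estimate of bias.

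**What to change.** Reconcile the Synopsis flow chart and its footnote 1 with sections 5.2.4, 5.2.5 and 14.2.1.1, so that one set of post-dose offsets appears everywhere. The offsets should be identical for all three doses, be counted from the actual vaccination date (the D28 and D56 visits carry a 4-day time window), and place the clinic assessment inside the solicited window. Align the laboratory days tied to D6, D36 and D63. Tabulate solicited events by dose over the common days, by date of onset. Which schedule applies is for the sponsor to settle.

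Cost: wording in the flow chart and these sections. Two clinic visits and their laboratory samples may move by one or two days. No visit is added.
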